15.1 Appendix 1 Patient information sheet and consent form……………………………………..……..20-25

15.2 Appendix 2 Topic Guides for data collection ……………………………………………………………….26-30

| 1. Background & Rationale In 2009, 189,100 abortions were carried out for women resident in England & Wales. 34% of these women had one or more previous abortions, an increase from 29% since 1998. The boroughs of Lambeth, Southwark and Lewisham have some of the highest rates of unplanned pregnancies and abortions in the UK. In 2009, there were 6,747 abortions amongst residents of Lambeth, Southwark and Lewisham with a rate of 34/1000 resident women between the ages of 15- 44 [1].This is nearly twice the national average abortion rate. 39% of these were repeat abortions.  The increase in repeat abortions is despite the widespread availability of contraceptive and emergency contraceptive services. This is a reflection of poor uptake and continuation of effective contraception post-abortion and highlights the gap between provision of abortion care and effective post-abortion care.  Reducing the number of repeat abortions remains a big challenge for the NHS. Several studies have attempted to investigate risk factors for repeat abortions to identify the high risk groups for targeted interventions [2-10]. Risk factors include young age, poor socio-economic status, unemployment, poor educational background, parous women, single/cohabiting with boyfriend, divorced/ separated/widowed women, multiple sexual partners, early age at sexual debut, unwanted sex, history of physical/sexual abuse, intimate partner violence, difficult schooling, defective parental images, geographic or social instability, psychological factors such as low self esteem, passivity, dependence, immaturity, depressive personality, previous psychiatric treatment, unstable relationships, failure to use contraception, associated with ambivalence in relation to desire for children or moral aversion to the use of contraception, non-attendance at follow up visits post-abortion, and non-participation of male partners in abortion decision-making.  Pregnancies ending in repeat abortions within a short time-frame are likely to be unintended pregnancies that might have been avoided. Abortion itself provides an opportunity for secondary prevention. The RCOG Guideline on abortion care recommends the provision of contraceptive advice as part of abortion counselling and the provision of a contraceptive method according to the woman’s choice to start straightaway after the abortion [11].  The London Sexual Health Strategic Framework has defined standards and outcome indicators for improving the Sexual Health of Londoners [12]. This includes the need to improve care pathways to promote post-abortion contraception with the aim of reducing repeat abortions. In accordance with this all abortion providers should be commissioned to provide contraception including Long acting methods of contraception (LARC) and all women leaving the service should be provided with one of the most effective methods of contraception (oral contraceptive pill, injection, Implant or Intrauterine device). Most of the abortion care in the NHS is contracted to the independent sector or provided by Hospital Trusts neither of whom hold ongoing responsibility for provision of continuing contraceptive care creating a disjunction between the two.  Previous studies have shown that contraceptive risk-taking is high both before and after abortion and that peri-abortion contraceptive counselling was ineffective or inadequate [13, 14]. A more thorough, client-centred & focussed peri-abortion contraceptive counselling with structured follow-up has been suggested by previously published research [15,16,17]. An audit of peri-abortion contraceptive counselling practices in a UK hospital showed that the content of contraceptive advice given to women undergoing abortion varied with only 40% receiving a comprehensive discussion on contraceptive options in relation to individual circumstances, and follow up had been arranged for less than half of the women [16].  A qualitative study of user experience of abortion services in Lambeth, Southwark & Lewisham highlighted the ineffectiveness of the system of peri-abortion contraceptive counseling, where there was no clarity about the roles of various service providers in provision of detailed and effective contraceptive counselling and follow-up, with a tendency for healthcare professionals to assume that the next person along the line would deal with contraception [14]. There was over-reliance on the ad-hoc post abortion follow up visit which the clients were expected to organize themselves.  Effective contraceptive counseling is time consuming especially for women who have already undergone an abortion as their contraceptive needs may be complex due to the various psycho-social aspects involved. It may be impractical to provide such counseling within the time available to staff during the referral visit, at the pre-abortion assessment or on the day of abortion. Moreover, women may not be in the right frame of mind to absorb all the information about contraception and make informed decisions during a stressful period.  A review of women presenting for repeat abortion within 24 months of the first abortion showed that although 58% accepted LARC following abortion, only 2% continued its use thereafter and 50% of women were not using any contraception at the time of abortion. Contraceptive counseling that educates them regarding expected side-effects of LARC and follow-up could ensure better compliance [18].  A recent study on abortion and repeat abortion in young women from London recommended the need for follow-up appointments for all young women undergoing abortion, which would address the whole woman and include intensive and individualized counseling based on their needs [19].  Focussing post-abortion care in a dedicated Specialty clinic providing contraceptive counseling has been shown to improve contraceptive uptake and reduce the incidence of repeat pregnancies [20].  Interventional studies that involved provision of a comprehensive specialist individualised contraceptive counseling & provision to women undergoing abortions have shown a better uptake of effective methods of contraception as compared to a package of limited information [21- 23]. Randomised studies of such interventions are scarce [21,23]. Specialist contraceptive advice on the day of abortion and enhanced provision had a short-lived effect on contraceptive uptake and increased the use of long-acting methods of contraception but did not appear to reduce repeat abortions [21].  A cohort study of women who underwent first trimester surgical abortions at a hospital based clinic in New York reported that women who returned for timely follow-up visits post-abortion were less likely to have subsequent repeat pregnancy and abortion in the 12 months post-abortion [24].  Lambeth, Southwark and Lewisham (LSL) jointly commission abortion services from 3 providers, King’s College Hospital NHS Trust, Marie Stopes International (MSI) and British Pregnancy Advisory service (BPAS). Provision of post-abortion contraception is included in the commissioning of abortion services. Specific structured follow-up for patients after the abortion to support contraceptive decision-making or contraceptive continuation is not routinely organized when women present for an abortion. Patients are advised to see their GP or referring doctor after 2 weeks for their routine follow-up. Patients may not be motivated to arrange such follow up if they have no problems related to the abortion itself.  In an effort to reduce the high rate of repeat abortions among young women in Lambeth, Southwark & Lewisham, there have been recent local pilot initiatives to try and follow up young women after their abortion to address their contraceptive needs. Evaluations of such an initiative from Lewisham providing follow up support to young women under the age of 18 during the period June 2008-June 2009, reported an impressive effect on uptake of reliable contraception post abortion, with the percentage of women relying on condoms alone following abortion falling to 17% as compared to more than 80% prior to abortion. Recommendations have been made by local Sexual Health Commissioners for follow up of young women under the age of 25 referred for abortion from Brook services and follow up of under 19 year old’s who have had more than 1 previous abortion or leaving the abortion provider without a method of contraception.  The aim of this research is to compare the effect of a specific intervention to provide contraceptive support following abortion with that of the existing arrangement of ad-hoc follow-up. The intervention will be in the form of a structured follow-up consultation either on telephone or face-face appointment as preferred by the woman with a Specialist in a Reproductive and Sexual Health service 2-4 weeks after the abortion with telephone follow-up 3 months after to provide further contraceptive support.  It is hypothesised that such a structured follow-up arrangement with the involvement of senior staff is more likely to result in better uptake and continuation of effective contraception as they would be able to unravel complex psycho-social factors that affect motivation and decision making regarding contraception. The follow-up consultations at 2-4 weeks and again at 3 months will offer the opportunity for women to discuss any issues or side-effects they may have in relation to their chosen contraceptive method. Women in the intervention group will be encouraged to bring along their male partners during the follow-up visit if they wished, as partners may play an important role in some cases in influencing motivation, contraceptive choice, compliance and continuation. Several previous studies have highlighted the benefits of involving male partners in post-abortion contraception counselling [25-29].  It is hoped that the findings from this study will have potential implications for policy decisions regarding meaningful  follow-up interventions to reduce repeat abortions. The economic costs of unplanned pregnancy are very high comparedwith the costs of prevention through effective provision and use of contraception [30]. If effective interventions tailored to the particular needs of this group can be determined and provided there is a potential for considerable savings to be made.  **References:**   1. Abortion Statistics, England and Wales: 2009 www.dh.gov.uk/publichealthstatistics 2. Heikinheimo O, Gissler M, Suhonen S. Age, parity, history of abortion and contraceptive choices affect the risk of   repeat abortion. Contraception. 2008 Aug; 78(2): 149-54.   1. Xu JS. Huang YM. Cheng LN. Factors in relation to repeated abortions among unmarried young people in Shanghai.   Chinese Journal of Epidemiology. 28(8):742-5, 2007 Aug.   1. Cheng YM. Wang XY. Lv YH. Cai YM. Li Y. et al. Study on the risk factors of repeated abortion among unmarried   adolescents. Chinese Journal of Epidemiology. 27(8):669-72, 2006 Aug.   1. Fisher WA. Singh SS. Shuper PA. Carey M. Otchet F. et al. Characteristics of women undergoing repeat induced   abortion. CMAJ Canadian Medical Association Journal. 172(5):637-41, 2005 Mar 1.   1. St John H. Critchley H. Glasier A. Can we identify women at risk of more than one termination of pregnancy?   Contraception. 71(1):31-4, 2005 Jan.  7. Addor V. Narring F. Michaud PA. Abortion trends 1990-1999 in a Swiss region and determinants of abortion  recurrence. Swiss Medical Weekly. 133(15-16):219-26, 2003 Apr 19.  8. Kitamura T. Toda MA. Shima S. Sugawara M. Single and repeated elective abortions in Japan: a psychosocial  study.Journal of Psychosomatic Obstetrics & Gynecology. 19(3):126-34, 1998 Sep.  9. Mattauer B. Peyrot D. Aussiloux MT. Repeated requests for termination of pregnancy. Some socio-cultural and  psychological aspects. Contraception, Fertilite, Sexualite. 12(4):573-80, 1984 Apr.  10. Blumenfield M. Psychological factors involved in request for elective abortion. Journal of Clinical Psychiatry.  39(1):17-25, 1978 Jan.  11. Royal College of Obstetricians and Gynaecologists (RCOG). Care of the Woman Requesting Induced Abortion.  London: RCOG, 2004  12. The London Sexual Health Strategic Framework, 2010, London Sexual Health Programme, London Specialised  commissioning Group  13. Palanivelu LM, Oswal A. Contraceptive practices in women with repeat termination of pregnancies.  J Obstet Gynaecol. 2007 Nov;27(8):832-4.  14. Kumar U. Baraitser P. Morton S. Massil H. Peri-abortion contraception: a qualitative study of users' experiences.  Journal of Family Planning & Reproductive Health Care. 30(1):55-6, 2004 Jan.  15. David PH. Reichenbach L. Savelieva I. Vartapetova N. Potemkina R.Women's reproductive health needs in Russia:  what can we learn from an intervention to improve post-abortion care? Health Policy & Planning. 22(2):83-94, 2007  Mar.  16. Garg M; Singh M; Mansour D Peri-abortion contraceptive care: can we reduce the incidence of repeat abortions?  Journal of Family Planning and Reproductive Healthcare 2001 Apr;27(2):77-80.  17. Osler M. Morgall JM. Jensen B. Osler M. Repeat abortion in Denmark. Danish Medical Bulletin. 39(1):89-91, 1992  Feb.  18. Das S, Adegbenro A. Ray S. Amu O. Repeat Abortion: Facts and issues.Journal of Family Planning & Reproductive  Health Care. 35 (2) : 93-5, 2009 Apr.  19. Lesley Hogart and Joan Philips. Policy Studies Institute. Government office for London. Dept. for children, Schools  and families. Young people in London: Abortion and repeat abortion. Research report  http://www.younglondonmatters.org/uploads/documents/tpyoungpeopleinlondonabortionandrepeatabortion.pdf  20. Masch R. Cabrera I. Adder R. et al The effect of consolidation of abortion services on patient outcomes.  Contraception. 77(1):60-3, 2008 Jan  21. Schunmann C. Glasier A. Specialist contraceptive counselling and provision after termination of pregnancy improves  uptake of long-acting methods but does not prevent repeat abortion: a randomized trial. Human Reproduction.  21(9):2296-303, 2006 Sep.  22. Johnson BR. Ndhlovu S. Farr SL. Chipato T. Reducing unplanned pregnancy and abortion in Zimbabwe through  postabortion contraception. Studies in Family Planning. 33(2):195-202, 2002 Jun.  23. Zhu JL. Zhang WH, Cheng Y. Xu J. Xu X. Gibson D. et al The Impact of post-abortion family planning services on  contraceptive use and abortion rate among young women in China : a cluster randomised trial. European Journal of . Contraception and Reproductive Health Care. 14 (1):46-54, 2009 Feb.   1. Madden T. Westhoff C. Rates of follow-up and repeat pregnancy in the 12 months after first trimester induced abortion. Obstetrics and Gynaecology. 113 (3): 663-8, 2009 Mar. 2. Becker S. Bazant ES. Meyers C. Couples counseling at an abortion clinic: a pilot study.   Contraception. 78(5):424-31, 2008 Nov.  26. Beenhakker B. Becker S. Hires S. Molano Di Targiana N. et al. Are partners available for post-abortion contraceptive . counseling? A pilot study in a Baltimore City clinic.Contraception. 69(5):419-23, 2004 May.  27. Holmgren K. Repeat abortion and contraceptive use. Report from an Interview Study in Stockholm.  Gynecologic & Obstetric Investigation. 37(4):254-9, 1994.  28. Blumenfield M. Psychological factors involved in request for elective abortion. Journal of Clinical Psychiatry.  39(1):17-25, 1978 Jan.  29. Luker K. Understanding the risk-taker. The Family Planner. 8(5-6):10-3, 1977.  30. McGuire A, Hughes D. The Economics of Family Planning Services; A report prepared for the contraceptive  alliance. Centre for Reviews and Dissemination, York 2008. |
| --- |

### 2 Research Objectives and Design

### 2.1. Research Objectives

| The objective of the study is to assess the impact of structured specialist follow-up after abortion to provide support to patients for contraceptive decision-making and continuation on the uptake and continuation of effective contraception at 6 months and the effect on repeat abortion at 1 and 2 years. |
| --- |

### 2.2 Research Design

| This will be a randomized controlled study with an intervention arm and a control arm.  **Control arm:** Patients who have undergone an abortion under the NHS in Lambeth, Southwark and Lewisham (LSL) who will be recipients of current standard follow-up practice post-abortion, which is routine advice to see their G.P. or referring clinician 2 weeks post-abortion.  **Intervention arm**: Patients who have undergone an abortion under the NHS in LSL who will receive a specific follow up consultation with a Specialist from the Reproductive and Sexual Health Service at King’s College Hospital either by telephone or a face-face clinic appointment depending on patient preference at 2-4 weeks post-abortion to discuss contraception and a telephone follow up 3 months post abortion to provide further contraceptive support. Women will be offered the opportunity to bring their male partners to the follow-up appointment if they wished, for participation in contraceptive counseling.  Any other follow up interventions aimed at young people outside of our research intervention that may happen as a result of local commissioning recommendations in LSL will apply to participants in both the control and intervention arms. Hence any biases related to such interventions will be attenuated by the randomization design of the study.  Verbal consent to send an information leaflet about the research study will be taken by the Central Termination of Pregnancy (TOP) Booking Service when patients phone for their abortion appointment. Written patient information about the research study will be sent to potential participants along with the details of their TOP consultation appointment. Patients who do not want any documentation posted to their home address, will be approached at their pre-abortion consultation visit by a trained member of staff and offered a patient information sheet and invited to take part in the study.  Written consent for participation in the study will be obtained from patients when they attend for their TOP consultation appointment. Study participants will be randomized to the intervention or control arm by pre-determined randomization codes for each centre (strata). The Randomisation codes will be held by the Chief Investigator based in the Reproductive and Sexual Health Service at King’s College Hospital.  Patients randomized to the intervention arm will be contacted by phone by the Research nurse/fellow during the week after their TOP procedure and offered the choice of a telephone consultation or a face-face clinic appointment with a Specialist in the Reproductive and Sexual Health service at King’s College Hospital 2-4 weeks post-abortion to provide contraceptive support. For patients who choose to have a telephone consultation, a suitable time slot for the consultation will be agreed and will receive their Specialist consultation by telephone during this time. For patients who prefer a face-face consultation, a suitable appointment will be arranged to see the Specialist 2-4 weeks post-abortion. Patients in the intervention arm will also be informed about the telephone follow-up at 3 months and 6 months post-abortion for contraceptive support.  Patients randomized to the control arm will be contacted by phone by the Research nurse/fellow only at 6 months to assess contraceptive uptake and continuation.  **Primary outcome measures**  Uptake and continuation of effective contraception at 6 months. Effective contraception will be defined as regular and consistent use of oral contraceptive pills/patches/vaginal ring (Nuvaring®)/ injectable contraception/ intrauterine contraception or the contraceptive implant. Use of barrier contraception or other methods such as withdrawal methods or natural family planning will not be considered as effective contraception due to their higher relative failure rates.  **Secondary outcomes**  Repeat abortion at 1 and 2 years. |
| --- |

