### 3.3 Selection of Participants

| Patients undergoing induced abortion (any gestation, all ages) under the NHS in Lambeth, Southwark or Lewisham with one of the three abortion providers - King’s College Hospital NHS Foundation Trust, British Pregnancy Advisory Service and Marie Stopes International, who have consented to participate in the study. |
| --- |

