**6.3 Analysis**

**Statistical analysis of primary outcome:** comparison of the binary outcomes (rates) in the two arms and adjusting for centres using Cochran-Mantel-Haenszel test.

**Statistical analysis of Secondary outcome**: comparison of the proportions (rates) in the two arms, Chi2 test, logistic regression and time-to-event analysis.

|  |
| --- |

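### The closed list that defines the primary endpoint omits female sterilisation and partner vasectomy, although the only reason given for excluding methods is a higher failure rate

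*Protocol*

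**What the plan says.** The primary outcome is uptake and continuation of effective contraception at 6 months. Section 2.2 says what counts: "Effective contraception will be defined as regular and consistent use of oral contraceptive pills/patches/vaginal ring" and, at the end of the list, "injectable contraception/ intrauterine contraception or the contraceptive implant". Nothing marks these as examples, and no clause admits methods of similar efficacy.

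The same section says what does not count: "Use of barrier contraception or other methods such as withdrawal methods or natural family planning will not be considered as effective contraception", and gives the reason: "due to their higher relative failure rates". Section 4.7 (Study end points) repeats both statements almost word for word.

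Section 6.3 plans a "comparison of the binary outcomes (rates) in the two arms and adjusting for centres using Cochran-Mantel-Haenszel test", so each woman is either a success or not. Section 3.3 admits "Patients undergoing induced abortion (any gestation, all ages) under the NHS in Lambeth, Southwark or Lewisham", and the exclusion criteria in section 3.2 do not mention sterilisation. Neither female sterilisation nor vasectomy appears anywhere in the protocol as shown, including the topic guides in Appendix 2. Topic Guide E does record, in both arms at 6 months, the method then in use.

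**The concern.** A closed list of successes combined with a binary outcome settles every unlisted method by default. A woman who has been sterilised, or whose partner has had a vasectomy, uses none of the listed methods and so counts as a failure. The only principle offered for leaving methods out is that they fail more often, and that is not a natural description of a permanent method. The rule and its rationale therefore give different answers for the same woman.

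This is more than detail that a protocol may leave to an analysis plan, because the protocol fixes the definition itself, twice. An analyst who applies the list as written misclassifies these women against the stated rationale. An analyst who recodes them departs from the written endpoint, which is hard to defend once results are known.

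**Working it through.** **1. Does the protocol's own sample size depend on this point?**

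Inputs from section 6.1: 68% in controls, a 15-point difference (so 83%), two-sided 0.05, 95% power, 223 per arm, 65% participation, 60% follow-up, 1144 in total.

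- Without continuity correction: n = [1.960 × √(2 × 0.755 × 0.245) + 1.645 × √(0.68 × 0.32 + 0.83 × 0.17)]² / 0.15² = 210.7, so 211 per arm.
- With continuity correction: (210.7 / 4) × [1 + √(1 + 4 / (210.7 × 0.15))]² = 223.8, so 224 per arm, against 223 stated. The figure reproduces. Power at 223 per arm without the correction is 96.0%.
- Total: 446 / 0.65 / 0.60 = 1143.6, so 1144. The centre figures agree: 618 + 366 + 160 = 1144.

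The 68% is described in section 6.1 as uptake of long-acting reversible methods or pills, and the 15-point target is set on the same measure. Neither figure counts permanent methods as successes, so omitting them from the endpoint list takes nothing away from 68% or 83%.

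**2. How does the endpoint classify each method?**

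| Method at 6 months | On the section 2.2 / 4.7 list? | Named as excluded? | Does the failure-rate reason fit? | Literal score |
|---|---|---|---|---|
| Pill, patch, ring, injectable, intrauterine, implant | Yes | No | Not applicable | Success |
| Barrier, withdrawal, natural family planning | No | Yes | Yes, as stated | Failure |
| Female sterilisation, partner vasectomy | No | No | No | Failure |

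The last row is the problem. The protocol quotes no failure rate for any method. The table assumes only that a permanent method does not fail more often than a daily pill.

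**3. What does the omission do to the comparison?**

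Let p_C and p_I be the proportions using a listed method in the control and intervention arms, and s_C and s_I the proportions relying on a permanent method instead.

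- Difference on the written list: p_I − p_C.
- Difference with permanent methods counted: (p_I + s_I) − (p_C + s_C).
- Change caused by the omission: s_I − s_C.

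Equal use in both arms lowers both rates and leaves the difference alone. Unequal use changes the difference by exactly the gap. No rate is given in the protocol, so the following is purely illustrative: with s_C = 1% and s_I = 1%, 2% or 3%, the written list understates the difference by 0, 1 or 2 points. With 223 women per arm, 1% is about 2 women (223 × 0.01 = 2.23).

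**The case against.** **The protocol never classifies sterilisation.** This is true. It is in neither the named successes nor the named exclusions, and a failure score follows from reading the list literally. A blinded coding rule for a rare method could settle it. But the success list is closed, while the excluded group is introduced with open wording, so the written rule points one way. A coding rule that pointed the other way would alter the endpoint rather than fill a gap.

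**A reversible or user-continued endpoint is a legitimate choice.** The Background cites a commissioning standard built on pill, injection, implant and intrauterine device. Section 6.1 works with reversible methods, and continuation and regular use suit methods that are started and kept up. This stands as a possible intention. It is not the reason the endpoint definition gives, and the definition does not restrict itself to reversible methods.

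**Few women would be affected.** This stands. All participants have just conceived, so reliance on sterilisation at 6 months would come almost entirely from recent procedures.

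**Two stronger readings are tempting.** A reader might infer a loss of power, for example by deducting 1 point from 68% and 3 from 83%: 67% against 80% at 223 per arm gives 87.8%. That double-counts, because the 68% never included permanent methods, and the 1% and 3% are invented. A reader might also infer that the primary comparison is biased towards no effect. The direction follows only if uptake is higher in the intervention arm. Counselling, the offer to bring partners and onward referral make that conceivable, but the protocol describes no sterilisation or vasectomy pathway and gives no sign that uptake differs by arm.

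**Conclusion.** The point holds as a flaw in the endpoint definition, and it is minor. The written list scores users of permanent methods as failures for no reason that the protocol gives. The consequence is misclassification of a probably small number of women. A shift in the treatment difference is conditional: it equals the gap between arms in permanent-method use, which the protocol neither states nor suggests, so no bias is shown. The sample size and power in section 6.1 stand.

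The conclusion rests on reading the list literally and on the assumption that permanent methods do not fail more often than the listed ones.

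**What to change.** Before outcome data are seen, add *female sterilisation or partner vasectomy* to the effective-method list in sections 2.2 and 4.7, coded from the current-method item in Topic Guide E. Leave the method set in section 6.1 as it is: it matches the source of the 68%, and widening it would detach the calculation from that source.

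If the endpoint is meant to cover reversible methods only, say so in both sections and give a reason other than failure rate.

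The cost is one phrase in two places. No new data item, visit or change in sample size is needed.
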